**Fig. 1 Fig1:**
[figure not shown]
Simulation of the dose escalation according to the occurrence of adverse events. Unless an adverse event is registered, dose escalation until the target dose will follow with each patient

### Patient population

Following inclusion criteria are required for participation:

Patients with ischemic as well as nonischemic cardiomyopathies.Implanted ICD or CRT-D.Prior ≥ 1 failed CA (with endocardial ± epicardial approach based on the substrate location and the ECG morphology of clinical VT) procedure to control sustained MMVT using currently recommended mapping and ablation techniques.Patients in whom ablation is not feasible or contraindicated (e.g. LV thrombus or mechanical mitral and aortic valve).MMVT recurrence after CA on optimized antiarrhythmic and heart failure medication.Age ≥ 18 years.IRB-approved, written informed consent as documented by signature.

Exclusion Criteria [17]:

Patients with MMVT who demonstrate:
Acute myocardial infarction.Primary electrical disease (channelopathy).Reversible and treatable cause (e.g., drug-induced or intoxication) of VT that can be adequately addressed otherwise.A target that cannot be safely and precisely defined based on stereotactic radiotherapy accuracy requirements (e.g., anatomical interference from OARs, overlapping prior radiation therapy to the thoracic region).Pregnancy or breastfeeding.Inability to provide informed consent.

### Follow-up

After study intervention, patients will be followed up after one day, one week, and at 3, 6, 9, 12, 18 and 24 months or if any symptoms occur necessitating work-up. Study assessments at the different follow-up timepoints are shown in Table 1.

**Table 1 Tab1:** Planned study assessments during follow-up

Follow-up	D1	W1	M3	M6	M9	M12	M18	M24
**Clinical examination**	X	X	X	X	X	X	X	X
**ECG**	X		X	X	X	X	X	X
**EP Map**	X							
**Lung function**	O			O				
**Chest/Cardiac-CT**	X		X			X		X
**FDG-PET**	O		O		O			O
**SPECT**	O		O		O			O
**MRI**	O		X		X			X
**Transthoracic echocardiography**	X		X		X			X
**ICD readouts**	X	O	X	X	X	X	X	X
**Medication use/dose**	X	X	X	X	X	X	X	X
**Blood samples**	X	O	O		O	O		O
**Chest X-ray**	O		O			O		
**CTCAE v5**	X		X	X	X	X	X	X
**PROMS**	X		X	X	X	X	X	X
**Physician reported QoL**	X		X	X	X	X	X	X

D = day; M = month; O = optional; PROMS = patient reported outcome measures; QoL = quality of life; X = mandatory; W = week. PROMS include EQ5D, SF-36, Treatment decision regret score

### Target definition and treatment delivery

All patients must undergo pre-procedural cardiac imaging (chest/cardiac CT).

Target volume delineation will be 4D-CT ITV based employing a 3–5 mm ITV to PTV margin. The ITV dose will be escalated from 27.0 Gy to an ITV prescription dose-equivalent level of maximum 35.1 Gy while keeping the PTV prescription dose constant at 25 Gy (Table 2). If feasible, software based electroanatomical mapping-to-radiotherapy planning registration will be employed [18]. The dose to the target (i.e. the VT substrate without PTV margin) will be increased by step-wise reduction of the prescribing isodose line (85% down to 65%).

Doses to OAR will be limited according to the recommendations published previously [19].

**Table 2 Tab2:** Summary of dose and fractionation schedules (all doses in Gy)

Level	PTV (D95%≥)	ITV (D95%≥)	Dmax (D0.1 cc)	Isodose
1	25.0 Gy	27.0 Gy	28.5–30.0 Gy	~ 85%
2	25.0 Gy	29.7 Gy	31.5–33.0 Gy	~ 75%
3	25.0 Gy	32.4 Gy	34.5–36.0 Gy	~ 70%
4	25.0 Gy	35.1 Gy	37.5–39.0 Gy	~ 65%

### Outcome measures

The primary outcome of this trial is safety measured by registered radiation associated adverse events (AE) up to 90 days after study intervention. This includes any radiation associated serious adverse event (SAE; at least grade 4 or 5 according to CTCAE v5), in particular death, radiation pneumonitis requiring hospitalization, radiation pericarditis requiring hospitalization and decrease in LVEF ≥ 10% as assessed by echocardiography or cardiac MRI. The secondary outcome measures include efficacy endpoints (i.e. freedom from sustained VT/VF), non-radiation associated safety and patient reported outcome measures (PROMS) as shown in Table 3.

**Table 3 Tab3:** Secondary outcome measures. QOL = quality of life

Efficacy	6-month survival free from electrical storm and incessant VT (binary endpoint) including an initial blanking period of 8 weeks
	Efficacy parameters will be assessed after an initial blanking period of 8 weeks, by comparing the 6 months prior to STAR with the 6 months after treatment, including the 8-week blanking period. All arrhythmic episodes occurring during the blanking period will be collected
	Sustained VT/VF burden as measured by number of post-treatment VT/VF episodes (ECG, ICD readouts). The main analysis will be performed by comparing the 6 months prior to STAR with the 6 months after treatment, which will include an 8-week blanking period
	Time to first sustained VT/VF recurrence as provided by ICD readouts, sustained VT/ICD shock and/or first VT storm
	Reduction of electrical storms and appropriate ATP and ICD shocks
	Need for antiarrhythmic drug use: type and dosages will be collected, and a drug index will be calculated
**Safety**	Overall survival and need for heart transplant or mechanical circulatory support: reported survival and heart transplant rates during follow-up
	Incidence of cardiac arrhythmic mortality or cardiac non arrhythmic mortality
	Non-radiation associated safety, e.g.: Hospitalization for acute heart failure necessitating inotropic therapy and if needed mechanical circulatory support except when other reason is apparent (e.g. acute coronary syndrome) ○ Cardiac tamponade ○ Major stroke or systemic embolism according to current diagnostic standards ○ ICD malfunction necessitating an interventional or operative approach
**Physician-reported and patient-reported QoL**	EQ5D, SF-35, QLQ-5, Treatment decision regret score
**Procedural technique outcome measures**	Error quantification of target definition and transfer from electrophysiology mapping to CT
	Correlation between dose to the target and VT number reduction
	Correlation between dose distribution to the target volume and scar formation
	Dose-volume constraints for OARs: as determined by organ-specific reported toxicity (CTCAE v5)
	The added value of additional imaging compared to standard CT imaging

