**Methods:**

Patients with ischemic or non-ischemic cardiomyopathy and recurrent sVA, with an ICD and history of ≥ 1 catheter ablation for sVA will be included. This is a prospective, multicenter, one-arm, dose-escalation trial utilizing the i3 + 3 design, a modified 3 + 3 specifically created to overcome limitations in traditional dose-finding studies. A total of 15 patients will be recruited. The trial aims to escalate the ITV dose from 27.0 Gy to an ITV prescription dose-equivalent level of maximum 35.1 Gy by keeping the PTV prescription dose constant at 25 Gy while increasing the dose to the target (i.e. the VT substrate without PTV margin) by step-wise reduction of the prescribing isodose line (85% down to 65%). The primary outcome of this trial is safety measured by registered radiation associated adverse events (AE) up to 90 days after study intervention including radiation associated serious adverse events graded as at least 4 or 5 according to CTCAE v5, radiation pneumonitis or pericarditis requiring hospitalization and decrease in LVEF ≥ 10% as assessed by echocardiography or cardiac MRI at 90 days after STAR. The sample size was determined assuming an acceptable primary outcome event rate of 20%. Secondary outcomes include sVA burden at 6 months after STAR, time to first sVA recurrence, reduction in appropriate ICD therapies, the need for escalation of antiarrhythmic drugs, non-radiation associated safety and patient reported outcome measures such as SF-36 and EQ5D.

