### Statistical analysis

We will perform intention-to-treat (ITT) and per-protocol (PP) analysis of the primary dataset using multivariate and subgroup analysis to evaluate safety, efficacy, OAR and target doses, and treatment strategies, and pair this with CTCAE events, QoL, and PROMs, as appropriate. The primary (safety outcome), toxicity, will be considered in a time-to-event fashion and a complication-free interval and complication-free overall survival will be estimated using the Kaplan-Meier method. Mortality will be presented as a Kaplan-Meier analysis curve. In addition, toxicity will be summarized in a graph as cumulative frequencies of the standardized toxicity levels for each time point. Statistical analysis of effectiveness (secondary analysis) will be performed by comparing the number of VT events, ICD shocks, and ATP events between the six months prior to the six month after the intervention. Effectiveness is described by measures of location and scatter (95% confidence intervals) of the distributions of the features and differences to baseline. In general, confidence intervals will be derived from the score function for proportions and Hodges-Lehmann intervals for medians. The statistical significance level will be two-sided, α = 0.05.

Adverse events will be tabulated by organ or sub-organ system, intensity, and relatedness. During data analysis, relevant stratification criteria are applied to the datasets. Notably, several arrhythmogenic life-threatening entities will be included to determine whether STAR is a ubiquitous treatment or whether certain conditions are more suitable for this innovative approach. VT affects both women and men, irrespective of any stratification criteria.

Missing data and dropouts will be dealt with as independent right censoring. Missing data will be listed, showing reasons for unavailability. Sensitivity analyses of efficacy endpoints will be performed on the per-protocol analysis set defined as the subset of the ITT analysis set who have received protocol treatment and who have no other major protocol deviations thought to impact on the efficacy conclusions of the trial. Only patients who discontinued the study due to consent withdrawal will be replaced with new patients and should get only standard follow-up and no further study-specific follow up.

Statistical analyses will be performed using R version 4.0.2 (The R Foundation of Statistical Computing, Vienna, Austria).

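### Table 3 leaves open whether episodes in the 8-week blanking period count in the before/after comparison; if they do not, raw counts show about a 31% reduction with no treatment effect

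*Protocol article*

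**What the plan says.** Three statements in the protocol article bear on this.

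- **Outcome measures, Table 3, general efficacy row.** "Efficacy parameters will be assessed after an initial blanking period of 8 weeks". The same sentence goes on to define the comparison as made "by comparing the 6 months prior to STAR with the 6 months after treatment, including the 8-week blanking period". The row then adds: "All arrhythmic episodes occurring during the blanking period will be collected". It does not say whether those episodes enter the comparison.
- **Outcome measures, Table 3, burden row.** Burden is a number of sustained VT/VF episodes. The main analysis sets the 6 months before STAR against "the 6 months after treatment, which will include an 8-week blanking period". The blanking period thus lies inside the six months and is not added to them.
- **Statistical analysis.** Effectiveness is analysed by "comparing the number of VT events, ICD shocks, and ATP events between the six months prior to the six month after the intervention". Blanking is not mentioned, and no rate or time-at-risk adjustment is given. The section also says: "The statistical significance level will be two-sided, α = 0.05". Missing data and dropouts are treated as independent right censoring.

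**The concern.** A blanking period ordinarily means that events in it are not counted, and Table 3 supports that sense by starting the assessment after it. If those weeks also lie inside the six-month post-treatment window, the post-treatment count covers less time than the pre-treatment count. A difference in raw counts then mixes any treatment effect with a difference in exposure, and the mixing favours STAR.

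The trial has one arm, so the before/after contrast is its stated effectiveness analysis, and sVA burden at 6 months comes first among the secondary outcomes in the abstract. If the handling stays open, it could be chosen after the data are seen, and the choice alone moves the null expectation by about 31 percentage points.

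A second problem does not depend on the blanking. A count up to month 6 is lower for anyone whose observation ends sooner, whatever the reason.

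**Working it through.** The article gives no expected reduction, effect size or power for this comparison, so there is no figure of its own to reproduce.

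**Inputs.** From Table 3: pre window 6 months (26 weeks), post window 6 months (26 weeks), blanking 8 weeks inside the post window, and a count as the metric. Assumed for the check: a constant event rate and no treatment effect.

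**Formula.** Expected post/pre count ratio = counted post time / counted pre time. Apparent reduction = 1 − ratio.

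| Handling | Counted post weeks | Ratio | Apparent reduction |
|---|---|---|---|
| A. Blanked episodes excluded, raw counts | 26 − 8 = 18 | 18/26 = 0.692 | 30.8% |
| B. Blanked episodes counted, raw counts | 26 | 26/26 = 1 | 0% |
| C. Blanked episodes excluded, events per week at risk | 18 | (18/18)/(26/26) = 1 | 0% |

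In days, the figure for A is 56/182.6 = 30.7%. It runs from 56/184 = 30.4% to 56/180 = 31.1%, depending on how six months is counted.

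**Early exit.** Take a patient with an unchanged event rate whose observation ends at week 13.
- Handling B: ratio 13/26 = 0.50, an apparent reduction of 50%.
- Handling A: ratio (13 − 8)/26 = 5/26 = 0.192, an apparent reduction of 80.8%.
- Per week at risk: 0% under both.

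**Illustration of the effect on a test.** Everything here except n = 15 and the two-sided 0.05 level is assumed: a Wilcoxon signed-rank test, patient rates drawn from a gamma distribution (shape 0.5 to 2), Poisson counts, and no true effect. Share of simulated trials rejecting under handling A with raw counts:

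| Assumed mean episodes per 6 months | Rejection rate |
|---|---|
| 5 | 35% to 44% |
| 10 | 59% to 69% |
| 20 | 82% to 93% |
| 50 | 97% to over 99% |

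With equal windows the same test rejected in about 4% to 6%. In a further run with mean 5 to 20 and within-patient overdispersion ranging from none to strong, handling A rejected in 19% to 89% of trials. The test on rates per week rejected in 4.5% to 5.0%.

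**The case against.** The strongest reply is that the article never says blanked episodes are dropped. Table 3 says twice that the post-treatment six months include the blanking period, says that all episodes in it are collected, and the Statistical analysis section compares six months with six months. On that reading the artefact is zero. This stands. A reader might infer that the plan builds in a 31% reduction, but the documents do not support that: it requires both that blanked episodes are excluded and that counts are not converted to rates, and neither is stated. What the reply cannot do is make Table 3 consistent. If every week counts, an assessment that begins after week 8 has no meaning.

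A reader might also take the simulated rejection rates as the plan's false-positive rate. They are not. The article names no test for this comparison. Hodges-Lehmann intervals for medians make the signed-rank test a plausible stand-in, but the event means and dispersion are assumptions, and the results vary widely with them.

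Third, these outcomes are secondary. The 15 patients rest on an acceptable toxicity rate of 20%, and neither the sample size nor the escalation rule uses this comparison. This also stands and limits the severity.

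Finally, details of exposure adjustment are commonly left to an analysis plan, dropouts are to be right-censored, and survival and transplant are reported separately. That answers part of the early-exit point. But right censoring works for a time-to-event outcome and does not by itself correct a raw count, and raw numbers are what the article specifies.

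**Conclusion.** The point holds in conditional form and should be fixed. The stated rule contradicts itself, and one natural way of carrying it out gives a biased effect. The size is about 31% (30.4% to 31.1%) if blanked episodes are excluded and raw counts are compared, and 0% if they are counted. Both figures assume a constant event rate and full follow-up to month 6. The early-exit problem exists under either reading. Its size depends on how many patients leave and when, which the article cannot tell us.

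The before/after counts are affected: VT/VF episodes, electrical storms, ATP, ICD shocks, and the planned correlation of target dose with reduction in VT number. The exposure imbalance does not reach the primary safety outcome, the binary 6-month endpoint or time to first recurrence, because none of these compares counts over two windows. It would be wrong to infer that the trial's main conclusion is at risk.

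**What to change.** Before the efficacy data are analysed:

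1. State in Table 3 and in the Statistical analysis section, in the same words, whether episodes in the first 8 weeks count in the main comparison.
2. Compare events per patient-week at risk, with exposure ending at death, transplant or loss to follow-up. If blanked episodes are excluded, exposure starts at week 9. Patients with no counted exposure should be listed, and deaths and transplants shown beside the rates, since a rate corrects for length of observation but does not make an early exit uninformative.
3. Report the other handling as a sensitivity analysis: all episodes from day 0, or week 9 to month 6.
4. Use the same rates in the correlation of dose with VT reduction.

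Moving the post window to weeks 9–34, so that 26 weeks face 26, is possible because mandatory ICD readouts are scheduled at months 6 and 9. It is optional, since it changes the stated 6-month endpoint of an ongoing trial.

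The cost is wording in two places and slightly more analysis work, with no new data. The stated reduction may turn out less favourable.

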## Background

Cardiovascular diseases account for 32% of deaths globally and 45% of deaths in Europe [1, 2]. Sudden cardiac death (SCD) caused by sustained ventricular tachycardia and fibrillation (VT/VF) account for approximately 50% of these death [3]. The most common causes for VT/VF are ischemic or non-ischemic (i.e. dilated, hypertrophic, etc.) cardiomyopathies (ICM, NIMC) that are associated with myocardial scar formation facilitating the development of arrhythmias.

While implantable cardioverter defibrillators (ICD) reduce the risk SCD due to VT/VF, they do not prevent their occurrence. Therefore, VT/VF remain major cause of morbidity and mortality as well as reduced quality of life in patients with ischemic or non-ischemic cardiomyopathies. Certain antiarrhythmic drugs (in particular amiodarone) and catheter ablation (CA) reduce the rate of VT/VF and SCD [3, 4]. But although CA is efficacious in suppressing sustained monomorphic VT (MMVT) a total recurrence rate of 33.2% was reported in a recent meta-analysis including all randomized controlled trials comparing CA with conservative treatment [5]. Difficulty in reaching arrhythmogenic substrate (intramural or epicardial), large scars and other procedural factors may lead to VT recurrence after an intervention. Additionally, CA can be associated with major complications in up to 9.5% [6].

More recently, stereotactic arrhythmia radioablation (STAR) has been introduced as a non-invasive treatment for refractory sustained MMVT with the delivery of a single fraction high-dose radiotherapy [7–9]. This treatment aims to deliver focal treatment to the arrhythmogenic substrate to ultimately induce transmural fibrosis, similar to the goal of CA.

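### The before/after VT counts and the 6-month storm endpoint take no account of rescue treatment after STAR, so part of its effect can be credited to STAR

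*Protocol article*

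**What the plan says.** The efficacy rows of Table 3 (Outcome measures) contain three kinds of VT endpoint:

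- **Counts.** The burden endpoint is "Sustained VT/VF burden as measured by number of post-treatment VT/VF episodes (ECG, ICD readouts"; electrical storms, appropriate ATP and ICD shocks are also listed. The Statistical analysis section fixes the comparison as "comparing the number of VT events, ICD shocks, and ATP events between the six months prior to the six month after the intervention".
- **Binary.** "6-month survival free from electrical storm and incessant VT (binary endpoint) including an initial blanking period of 8 weeks".
- **Time to event.** "Time to first sustained VT/VF recurrence as provided by ICD readouts, sustained VT/ICD shock and/or first VT storm".

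On blanking, Table 3 says "Efficacy parameters will be assessed after an initial blanking period of 8 weeks". The same row says that the 6 months after treatment include the 8 weeks and that all episodes in that period will be collected.

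The article expects further treatment after STAR. The abstract lists "the need for escalation of antiarrhythmic drugs" as a secondary outcome, and Table 3 adds a drug index. Its safety rows list "Overall survival and need for heart transplant or mechanical circulatory support". The Background states: "Certain antiarrhythmic drugs (in particular amiodarone) and catheter ablation (CA) reduce the rate of VT/VF and SCD". None of these is linked to the VT endpoints. Repeat catheter ablation after STAR appears in neither Table 1 nor Table 3.

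**The concern.** In a randomised comparison, rescue treatment would occur in both arms and could be interpreted against a control. Here each patient is compared only with his or her own previous 6 months. If VT recurs after STAR and is then suppressed by another ablation or more drug, the post-treatment count falls for a reason other than STAR, and nothing in the comparison separates the two.

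The binary endpoint has the same weakness. An ordinary VT recurrence is not a storm or incessant VT, so it can prompt rescue before the endpoint is reached. Blanking adds to this: a recurrence in week 4 may be left out while the benefit of the treatment given for it is counted.

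What is at stake is how the secondary efficacy results are read. They bear on the stated aim of finding the minimal efficacious dose, because Table 3 also plans to correlate target dose with the reduction in VT number, and that correlation uses the same counts.

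**Working it through.** **The plan's own figure.** The article gives no target, effect size or power for any VT endpoint. Its only sample-size figure, 15 patients with an acceptable toxicity rate of 20% ±5, concerns safety. There is no efficacy figure to reproduce, and N does not depend on this point.

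**Inputs.**
- From the article: n = 15; a 6-month window; 8 weeks of blanking (56/30.4375 = 1.84 months); two-sided α = 0.05.
- From the Background, used only as upper bounds: recurrence after STAR in up to 75% within a year, so rescue share f ≤ 0.75; recurrence after catheter ablation of 33.2%, so rate reduction from rescue r ≤ 1 − 0.332 = 0.668.
- Assumed: f = 0.25 to 0.75, r = 0.3 to 0.668, month of rescue t = 1 to 3. The formulas also assume that rescued patients have the same average VT rate as the others.

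**Formulas, with no STAR effect.**
- Full window counted: apparent fall = f × r × (6 − t)/6.
- Only episodes after blanking counted: apparent fall = f × r × (6 − max(t, 1.84))/(6 − 1.84).

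| f | r | t (months) | Full window | After blanking |
|---|---|---|---|---|
| 0.25 | 0.3 | 3 | 0.25 × 0.3 × 3/6 = 4% | 5% |
| 0.25 | 0.5 | 2 | 0.25 × 0.5 × 4/6 = 8% | 12% |
| 0.5 | 0.5 | 2 | 0.5 × 0.5 × 4/6 = 17% | 24% |
| 0.75 | 0.5 | 2 | 0.75 × 0.5 × 4/6 = 25% | 36% |
| 0.75 | 0.668 | 1 | 0.75 × 0.668 × 5/6 = 42% | 50% |

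The first and last rows are the extremes of the grid.

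A single example shows how much timing matters. Suppose 5 of 15 patients have drug escalation that halves their rate. If it starts at month 2 and the full window counts, the fall is 5/15 × 0.5 × 4/6 = 11%. If it starts within the blanking period and only later episodes count, the fall is 5/15 × 0.5 = 17%.

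**Chance of a significant fall with no STAR effect.** This was simulated with n = 15, a Wilcoxon signed-rank test, two-sided 0.05, 4,000 runs, rescue at month 2 and the full window counted. The assumed mean was 10 episodes per 6 months, with gamma heterogeneity of shape 1.

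| f | r | Significant fall |
|---|---|---|
| 0 | – | 2.3% |
| 0.25 | 0.5 | 7.8% |
| 0.5 | 0.5 | 21.5% |
| 0.75 | 0.5 | 44.5% |
| 0.75 | 0.668 | 60.5% |

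**Which endpoints are exposed.**
- Burden, ATP and shocks: exposed whenever rescue is given inside the 6 months.
- Storm/incessant VT: exposed when rescue follows a lesser recurrence or a blanked event. Death already counts as failure, because the endpoint is survival free of these events.
- Time to first recurrence: treatment given after a counted recurrence cannot change it. It is exposed only when the recurrence is blanked and rescue then delays the next one.

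**The case against.** The strongest objection is that the article never says episodes are counted through rescue. That is inferred from a fixed 6-month window, an intention-to-treat analysis and the absence of any condition, and a fuller protocol or analysis plan may hold a rule. This stands as a limit on wording. However, the article does fix the window and the comparison, and stopping the count at rescue would depart from them, so counting through is the natural reading.

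Other arguments on that side:

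- **The confounding would be visible.** Medication is recorded at every visit, and the drug index and transplant are reported. This is true for drugs and transplant, but nothing ties them to the VT endpoints, and the article does not list repeat ablation.
- **Other analyses might cover it.** The per-protocol set does not name rescue as a deviation. If it did, dropping rescued patients would remove STAR failures. The multivariate analysis cannot adjust much with 15 patients over four dose levels. Transplant might fall under independent right censoring; the text does not say, and such censoring would be informative.
- **Including later treatment is a legitimate estimand.** This stands, and is why the stated count should be kept. Stopping the count at rescue also shortens follow-up in exactly the patients who are failing.

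A reader might infer three stronger claims that the documents do not support. The first is that every VT endpoint is affected; time to first recurrence mostly is not. The second is that the bias always favours STAR. It does so when rescue follows recurrence, but drug reduction after STAR would push counts the other way. The third is a firm loss on the success rate: taking 3 re-ablated patients and the 33.2% figure gives 3 × 0.668/15 = 13 points. That assumes that all three would otherwise fail, and it applies an any-recurrence rate to a storm endpoint.

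**Conclusion.** The point holds for the before/after counts and the 6-month storm/incessant-VT endpoint. As defined, they let the effect of rescue given after a recurrence be credited to STAR, and no other part of the article removes this. It holds for time to first recurrence only after a blanked recurrence.

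The size cannot be read from the documents. The range of 4% to 42% (5% to 50% if only episodes after blanking count) rests wholly on assumed rescue share, effect and timing, with the article's recurrence figures serving only as bounds. The simulated error rates also depend on the assumed episode distribution. All affected endpoints are secondary, so this should be changed but does not threaten the safety question.

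**What to change.** 1. **Binary endpoint.** Count repeat catheter ablation, repeat STAR and transplant or mechanical support as failure from day 0, blanking period included. Report a second version that also counts escalation of antiarrhythmic drugs, for recurrent VT, above the dose at STAR. Restricting this to escalation for recurrent VT avoids penalising changes made for other reasons.
2. **Counts.** Keep the stated 6-month comparison. Add a sensitivity analysis of VT, ATP and shock rates up to first rescue, using exposure time, and state that this truncation is informative.
3. **Data.** Record repeat ablation as an outcome, and date it. Date drug changes too, since no visit is scheduled between week 1 and month 3.

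The cost is outcome wording, a small addition to the case report form and slightly more analysis. Drug type and dose are already collected. The downside is a less favourable success rate. The primary safety outcome, N = 15 and patient care do not change.

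### The fixed 6-month baseline for VT burden can include episodes from before the last ablation or drug change, so their effect can be credited to STAR in the secondary efficacy analyses

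*Protocol article*

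**What the plan says.** Table 3 of the protocol article (Outcome measures, Efficacy) defines the main VT/VF burden analysis: "The main analysis will be performed by comparing the 6 months prior to STAR with the 6 months after treatment". The Statistical analysis section repeats the window and makes clear that counts are compared: "comparing the number of VT events, ICD shocks, and ATP events between the six months prior to the six month after the intervention".

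The inclusion criteria (Patient population) ask for "Prior ≥ 1 failed CA (with endocardial ± epicardial approach based on the substrate location" and for "MMVT recurrence after CA on optimized antiarrhythmic and heart failure medication". Neither carries a date or a minimum time before STAR. The same list also contains "Patients in whom ablation is not feasible or contraindicated", without saying whether this is an alternative to the failed ablation. The abstract (Methods) describes all patients as having had one: "with an ICD and history of ≥ 1 catheter ablation for sVA will be included".

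Antiarrhythmic drug use is a separate outcome in Table 3, where "type and dosages will be collected, and a drug index will be calculated". The article does not say that the before-after comparison takes drug changes or the ablation date into account. The trial has one arm, and the abstract gives its size: "A total of 15 patients will be recruited".

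**The concern.** The baseline window and the entry criteria can overlap. A patient ablated 2 months before STAR is eligible as the article is written. That patient's baseline then holds 4 months from before the ablation and only 2 months of the state in which STAR is given. An ablation that failed, in the sense that VT came back, may still have changed how often VT occurs. The same applies to drug optimization. The article's own Background section says that ablation and certain antiarrhythmic drugs lower the VT/VF rate, so the mechanism is one the sponsor accepts.

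There is no control arm to absorb such a change. The readouts exposed are the before-after differences in VT/VF episodes, ATP, shocks and storms. The correlation between target dose and VT number reduction (Table 3, procedural technique outcomes) uses the same differences. With 15 patients over four dose levels, unequal intervals from ablation to STAR could mimic or hide a dose effect. This matters because the Background section names the minimal efficacious dose as an aim.

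**Working it through.** The article states no effect size, VT rate or power for VT burden, so there is no planned figure to reproduce. The check asks what the planned comparison would show if STAR did nothing.

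**Inputs from the article:** 6 months before and 6 months after STAR; counts; one arm; 15 patients; two-sided 5% level.

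**Assumptions, none given in the article:** the last ablation or drug change falls k months before STAR (k between 0 and 6), and from then on the episode rate is f times the earlier rate and stays constant.

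**Formula.** With the earlier rate set to 1 per month:
- baseline count = (6 − k) + f·k
- count after STAR = 6·f
- apparent reduction = 1 − 6f / [(6 − k) + f·k]

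For k = 2 and f = 0.5: baseline 4 + 1 = 5, after STAR 3, apparent reduction 1 − 3/5 = 40%.

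Apparent reduction with a STAR that has no effect:

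| Rate after the change (f) | k = 1 | k = 2 | k = 3 | k = 4 | k = 5 | k ≥ 6 |
|---|---|---|---|---|---|---|
| 0.75 | 21.7% | 18.2% | 14.3% | 10.0% | 5.3% | 0% |
| 0.50 | 45.5% | 40.0% | 33.3% | 25.0% | 14.3% | 0% |
| 0.25 | 71.4% | 66.7% | 60.0% | 50.0% | 33.3% | 0% |

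A weaker change, k = 2 and f = 0.8, gives 1 − 4.8/5.6 = 14%.

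**Opposite direction.** The bias need not favour STAR:
- If the rate rose after the change, k = 2 and f = 1.5: baseline 4 + 3 = 7, after STAR 9, and 1 − 9/7 = −29%, an apparent increase.
- If the rate was not constant, for example ablation 2 months before STAR, one quiet month, then the old rate: baseline 4 + 0 + 1 = 5, after STAR 6, and 1 − 6/5 = −20%.

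**Dilution across the cohort.** Take k = 2, f = 0.5 and the same current rate in every patient. An affected patient has a baseline of 5, an unaffected one 6 × 0.5 = 3, and both have 3 after STAR. If one third are affected, the mean baseline is 5/3 + 2 = 3.67 and the apparent reduction is 1 − 3/3.67 = 18%. If two thirds are affected, it is 10/3 + 1 = 4.33 and 31%.

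**Chance of a false claim.** This was simulated with 15 patients, overdispersed (gamma-Poisson, dispersion 1) counts, no STAR effect, k = 2, f = 0.5 and 1000 runs per setting. The test was a paired Wilcoxon test at two-sided 0.05; the article names no test for this comparison, so that choice is an assumption too.

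| Share of patients with the change in the window | 1 episode/month before the change | 4 episodes/month before the change |
|---|---|---|
| 0% | about 5% | about 5% |
| 33% | about 11% | about 22% |
| 67% | about 34% | about 68% |
| 100% | about 66% | about 98% |

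These error rates hold only for a rate that fell by half and stayed there.

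**The case against.** The strongest case against is that this is a possibility, not an established bias. It needs patients whose last ablation or drug change fell within 6 months of STAR, and it needs that change to have altered the VT rate. The article gives neither figure. These patients are selected because ablation failed and VT recurred, so no change, a rise, or a quiet spell followed by return are all plausible. The last two push the bias against STAR. This stands. A reader might infer that the plan does count pre-ablation episodes and does credit their decline to STAR, but the article supports only that it can.

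A second objection concerns the remedy. It is tempting to move the main baseline to the day after the last ablation, but that window is selected too. In the quiet-spell example it would give 1 episode-unit in 2 months, or 0.5 per month, against 1 per month after STAR: an apparent doubling with no STAR effect. A baseline of a few weeks that must contain the qualifying recurrence can instead overstate the rate and favour STAR. This also stands, so replacing the main analysis is not justified.

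Third, effectiveness is a secondary analysis. Sample size rests on the toxicity rate and escalation on dose-limiting toxicities. Event-free survival at 6 months and time to first recurrence need no baseline count. All of this is right and limits the scope. The criterion on infeasible or contraindicated ablation may also admit some patients with no ablation in the window, although the abstract suggests otherwise.

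Finally, the full protocol or SAP may deal with ablation dates. That is possible. But the point is not that a detail is absent: the article fixes the window in two places, and an analysis that follows that text carries the problem.

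**Conclusion.** The point holds in conditional form. The fixed 6-month count baseline, with no minimum interval from the last ablation or drug optimization, can mix the effect of earlier treatment into the apparent effect of STAR. Under a rate that halved 2 months before STAR and stayed there, the spurious reduction is 40% in an affected patient. Over the range f = 0.25 to 0.75 and k = 1 to 5 it runs from about 5% to 71%. It is zero, within this constant-rate model, if the change lies at least 6 months back or did not alter the rate. It reverses sign if the rate rose or VT returned after a quiet spell. The cohort-level size depends on the share of affected patients, which is not stated.

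The reach is limited to the secondary before-after efficacy counts and the dose versus VT-reduction correlation. A reader might infer that the safety conclusion or the escalation decisions are compromised. They are not, because neither uses these counts.

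**What to change.** Keep the 6-month comparison as the main analysis and add two sensitivity analyses to the Statistical analysis section:

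- (a) the same comparison restricted to patients with no catheter ablation and no major antiarrhythmic drug change in the 6 months before STAR;
- (b) episodes, ATP and shocks as rates per device-monitored month, with the baseline starting after the last ablation or major antiarrhythmic drug change.

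Define beforehand what counts as a major drug change. Report the time from last ablation to STAR for each patient, and show it beside the dose versus VT-reduction correlation. If (a) or (b) differs materially from the main analysis, qualify the efficacy conclusion accordingly. Eligibility and treatment do not change.

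**Cost:** some added wording, two analyses, and the dates of the last ablation and last drug change. The article does not list these dates as collected items, but ablation history and medication are needed to judge eligibility, and device records are needed for the planned baseline anyway.

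**Downside:** (a) may leave few patients; if a third of the 15 were affected, 10 would remain, and if two thirds, 5. In (b) the baseline may be short and noisy, and distorted by selection on recurrence or by a quiet spell after ablation. Neither should therefore be read alone; what is informative is whether they agree with the main result.
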